### Sample size calculation

The study is designed to demonstrate a clinically relevant difference regarding time to complete epithelialization between the treatment arms. Based on a retrospective study of 70 patients with superficial and deep partial thickness burns of the hand, we expect wounds to heal in 11 days on average with Flamazine**®** and in 6 days on average with Flaminal**®** (pooled standard deviation 7.5 days) [28]. With alpha set at 5 %, 41 patients are needed in both intervention arms to detect a difference in wound healing time with 80 % power. To allow for 10 % attrition, a total of 90 patients will be included in the study.

### Statistical analysis

The analysis will be performed according to the intention-to-treat principle. The baseline patient characteristics will be described as mean ± standard deviation for normally distributed continuous variables, as median (range) for skewed continuous variables, and as number (proportion) for categorical variables. Differences in time to complete re-epithelialization will be compared in both treatment groups will be analyzed with Kaplan-Meier curves and log rank test.

If the baseline characteristics seem unbalanced despite randomization, a multivariable Cox regression analysis will be performed to correct for potentially confounding variables to confirm the primary analysis.

The secondary clinical and patient-reported outcomes on specific follow-up moments will be compared between the treatment groups using the two-sided *t* test or Mann-Whitney test for continuous data, and a two-sided Chi-square test or Fisher’s exact test for categorical data. Repeatedly measured study parameters such as pain and quality of life will be also analyzed using a linear mixed model with treatment as fixed effect and patient as random effect. In the analyses, *p* values <0.05 will be considered statistically significant.

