### Study population

The study will be performed in two of the three burn centers (Beverwijk and Rotterdam) in The Netherlands. In these burn centers, both Flaminal® and Flamazine® are therapeutic options for treating partial thickness burns. Patients who are admitted to the Beverwijk or Rotterdam Burn Centre and who meet the following inclusion criteria will be eligible for this study: competent or temporarily non-competent (because of sedation and/or intubation); partial thickness burns of minimally 1 % total body surface area (TBSA) (possibly in combination with full thickness burns); hospital admission within 48 hours of burn injury; written informed consent by the patient. Patients meeting one or more of the following criteria are excluded: age below 18 years; TBSA of more than 30 %; burns caused by chemicals, electricity or radiation; if local therapy with a topical agent has already started; patients who are expected (according to the treating medical physician) to be non-compliant with the study protocol.

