### Recruitment, consent and randomization

All patients who are admitted to the burn center undergo standardized screening and baseline procedures according to the local protocol. The local investigator will check the inclusion and exclusion criteria of the study and will inform the participant about the study. If the participants are willing to participate in this study, they must provide written informed consent. If an eligible patient is temporarily non-competent because of sedation and/or intubation, a legal representative of the patient, according to the Dutch Medical Treatment Act (WGBO), will be informed about the study and will provide written informed consent. After the sedation or intubation has ended, the patient will be asked to confirm willingness to participate in the study in writing, otherwise the participation is discontinued and the collected study data will be destroyed.

After informed consent has been obtained, the largest partial thickness area will be assigned as the study area. Thereafter, the patient will be randomly assigned to one of the two study arms using TenALEA (Trans European Network for Clinical Trials Services), an online randomization program (www.flam-studie.nl). The online-randomization is stratified by center and uses variably sized blocks in a 1:1 ratio. In both participating hospitals the local trial coordinator will receive a username and password for online randomization. After randomization the local trial coordinator of that center and the central trial coordinator will receive an email with the inclusion number and the randomization outcome. The outcome will also be displayed on the website, only visible for the randomizing local and central trial coordinators. Then, all the burn wounds will be treated with the treatment that is assigned by the randomization.

When the study area that was initially assessed as a partial thickness burn, turns out to be a full thickness burn area after performing laser Doppler imaging (LDI), then the study area will be replaced: the second largest partial thickness area (confirmed by LDI) will then be chosen as the study area.

For practical reasons it is not possible to blind the patients. It is also impossible to blind the medical staff who provide the burn wound care, because they are involved in all aspects of the care and are able to recognize each treatment from its appearance. No blinding of other outcomes is also possible for the same reasons.

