
After discharge, patients in both group will be treated in an outpatient setting, according to the local protocol.

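### Randomization is stratified by center, but the analyses as described do not use center: a minor and conditional loss of efficiency, not a threat to validity

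*Protocol article*

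**What the plan says.** Under Study population: "The study will be performed in two of the three burn centers". Under Recruitment, consent and randomization: "The online-randomization is stratified by center and uses variably sized blocks in a 1:1 ratio". Center is the only stratification factor named.

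Under Statistical analysis, the primary outcome is to be "analyzed with Kaplan-Meier curves and log rank test", with no mention of center. Adjustment is conditional: "If the baseline characteristics seem unbalanced despite randomization, a multivariable Cox regression analysis will be performed to correct for potentially confounding variables". The variables are not named, and this model serves to confirm the primary result. The mixed model for pain and quality of life is described with a fixed effect for treatment and a random effect for patient, and no other term.

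Under Interventions, patients in both arms, once discharged, "will be treated in an outpatient setting, according to the local protocol".

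**The concern.** If a factor is balanced by design and also predicts the outcome, an analysis that leaves it out loses in two ways. Its variance estimate still contains between-center variation that the balanced allocation has already removed from the comparison, so the test rejects too rarely under the null. And when two centers with different healing rates are pooled, the marginal hazard ratio moves toward 1, so the test also detects less.

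The written plan leaves center little room to enter. The Cox model depends on an observed imbalance, and center is the one variable that the randomization keeps balanced. If another imbalance triggers the model, nothing says that center goes in. At stake is some power in a trial of 90 patients planned at 80 % power.

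Healing could differ between the centers for reasons that the article allows: care after discharge follows local practice, and the depth classes in Table 1 run from healing within 14 days to healing beyond 21 days or not at all, so the two centers may have a different case mix. The article does not say that they do.

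**Working it through.** **The plan's sample size.** From Sample size calculation: "we expect wounds to heal in 11 days on average with Flamazine", "in 6 days on average with Flaminal", "pooled standard deviation 7.5 days", alpha 5 % (taken as two-sided), power 80 %.

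- Normal formula: n = 2 × [7.5 × (1.960 + 0.842) / 5]² = 35.3, so 36 per arm.
- Divided by 0.864, the lower bound of the Mann-Whitney test's efficiency relative to the t test: 35.3 / 0.864 = 40.9, so 41 per arm, as stated. The article does not name this step; 85 % power in the normal formula also gives 41.
- Total: 2 × 41 = 82; 82 × 1.10 = 90.2, about 90.

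The check below uses the 82 patients before attrition.

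**Treatment effect assumed.** With D events and 1:1 allocation, log-rank power ≈ Φ(√(D/4) × ln HR − 1.96). For D = 82 and HR = 1.86 this is Φ(4.528 × 0.621 − 1.96) = Φ(0.85) = 80 %. So 1.86 is the hazard ratio that matches the planned power. The plan's ratio of means, 11/6 = 1.83, would give 78 %.

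**Simulation.** Exponential healing times, all 82 patients heal, exact 1:1 allocation within center, two-sided 5 % tests. The centers hold 40 and 42 patients (about 50:50) or 56 and 26 (about 70:30, the smaller center healing faster). There were 4,000 runs per scenario, so the Monte Carlo standard error is about 0.7 points for power and 0.3 points for a rate near 5 %. The center hazard ratios are assumptions; the documents give none.

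Power (%), log-rank test without and with stratification by center:

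| Center HR | 50:50 without | 50:50 with | 70:30 without | 70:30 with |
|---|---|---|---|---|
| 1.0 | 77.8 | 76.1 | 78.6 | 77.2 |
| 1.25 | 78.3 | 77.4 | 77.8 | 77.1 |
| 1.5 | 75.0 | 75.7 | 76.0 | 75.9 |
| 2 | 69.3 | 74.3 | 74.0 | 77.5 |
| 3 | 62.9 | 76.3 | 69.3 | 77.3 |

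The loss from not stratifying is 5.0 and 3.5 points at a center HR of 2, and 13.4 and 8.0 points at 3. A repeat with 20,000 runs gave, at 2, 72.0 against 76.8 % (50:50) and 73.5 against 76.6 % (70:30); at 3, 64.0 against 76.5 % and 69.0 against 76.6 %. Those are losses of 4.8, 3.1, 12.5 and 7.6 points.

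**No treatment effect.** Over the same scenarios the unstratified test rejected in 2.8 to 5.8 % of runs and the stratified test in 4.9 to 5.8 %. At a center HR of 3 the unstratified rate was 2.8 % (50:50) and 4.3 % (70:30); with 20,000 runs it was 3.4 % and 4.2 %. Ignoring center pushes the rate down, not up.

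**The case against.** The strongest objection is that this is read from silence. The text is a condensed journal article. It never says that the log-rank test is unstratified, and the analysis plan, which is not shown, may stratify it. That limits the point: one cannot conclude that the trial will ignore center. It does not remove it. The article does set out where adjustment enters, and the imbalance trigger and the two-term mixed model both pass center by.

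Second, nothing here is invalid. A reader might infer that the primary p value is wrong or that false positives become more likely. The simulations show the reverse, so this part of the objection stands in full.

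Third, the loss needs a large center difference. Even a center HR of 2 exceeds the ratio of 1.83 in the plan's own treatment contrast, and the documents report no difference at all. Regimens, the rule that two specialists must agree on healing, and the training in laser Doppler imaging are common to both centers. A reader might also infer that grafting follows center-specific rules. The outcome section does not support this: it gives one timing window and one set of reasons for both centers. Only care after discharge is local, and the article does not say how much healing falls in that period. So the size of the benefit is unknown.

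**Conclusion.** The point holds as a minor efficiency improvement. The design uses center and the analyses as described do not. The unstratified log-rank test remains valid, and turns conservative and weaker only if healing differs markedly between centers. The loss is negligible up to a center HR of about 1.5, about 3 to 5 points of power at 2, and about 8 to 13 points at 3. It would be wrong to say that any center difference costs power: if the centers are alike, the stratified test is the slightly weaker one.

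The figures rest on exponential times, 82 events, a treatment HR of 1.86, a constant center effect and the two center splits shown. Patients who do not heal or are censored would reduce the events and change the absolute power. The mixed-model part rests on the same reasoning and was not simulated.

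**What to change.** State in the statistical section, or confirm in the analysis plan, that the primary test is a log-rank test stratified by center, that any Cox model is stratified by center, and that the mixed models include center as a fixed effect. Settle this before outcomes are compared by arm.

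The change takes a few words and no new data, since center is known for every patient and there are only two strata. The statistical cost is about 1 to 2 points of power if the centers heal alike, against the gains above if they differ about twofold or more.

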#### Secondary outcomes/study parameters

o*Clinical outcomes:*Need for operation which is evaluated between 10 and 14 days post burn. Reasons for operation are that the experienced burn specialist expects no further wound healing in the next 7 to 11 days of the partial thickness area or a full thickness burn. If the decision to graft is made before 10 to 14 days post burn then the operation will still performed before 10^th^ day post burn day. The only indication for operation before the 10^th^ PBD is when a partial thickness burn becomes a full partial thickness burn. The treatment of full thickness burns is split skin graft in an early stagePercentage TBSA of the study area that covered with skin graftColonization: twice a week a wound swab will be taken from the study area. The wound swab will then be sent for laboratory investigation. In brief, the analysis of the wound swab will include the following steps. The microscopic examination will entail gram-staining. Thereafter, a quantity of the specimen will be cultured to obtain a pure single specimen culture. Finally, the sensitivity of the organisms to specific local therapy will be determined. In case of wound colonization the treatment will be changed to another relevant treatment based on the results of the wound cultureInfection: infection is suspected if a combination of skin redness, pain, swelling, tenderness, warmth, fever or pus draining from the wound is present. Infection is a clinical evaluation of the wound, in presence of absence of positive wound culture, and is judged by a physician at the burn center during each dressing changeNumber of dressing changesUse of systemic antibioticso*Patient-reported outcomes:*Pain will be measured during the application and removal of the wound dressing (procedural pain, measured directly after dressing change) and background pain (measured in the morning and evening). Pain will be measured twice daily during hospital admission by use of a Visual Analogue Thermometer (VAT), which is a numeric scale from 0 (no pain) to 10 (worst imaginable pain)Itching will be measured daily in the evening during hospital admission by use of a VAT [31]Anxiety: the Burn Specific Pain Anxiety Scale (BSPAS) will be scored on day 7 ± 2 post burn and on the day of discharge. The BSPAS is a valid and reliable nine-item self-report scale for the assessment of pain-related and anticipatory anxiety in burned patients [32, 33]Health-related quality of life (HRQoL) will be measured using the following questionnaires, in the week before discharge and at 3, 6 and 12 months post burn:Burn-specific quality of life (QoL) will be measured using the Dutch version of the Burn Specific Health Scale (BSHS)–Brief [34, 35]. The BSHS-Brief is a valid and reliable self-administered questionnaire that covers nine domains (heat sensitivity, affect, hand function, treatment regimens, work, sexuality, interpersonal relationships, simple abilities, and body image). The questionnaire takes 10–15 minutes to complete and 5 minutes to score. Responses are scored by the patient on a five-point scale from 0 (extreme) to 4 (none/not at all) for each of the 40 items. Mean scores are calculated for each of the domainsGeneral HRQoL will be measured using the EuroQol-5D (EQ-5D) questionnaire [36]. This simple and generic description of health status is widely used in studies on clinical and economic appraisal. The EQ-5D outcomes will be converted in utility scores between 0 (death) and 1 (perfect health) based on empirical valuations [37]. From the area under the utility curve during the 12 months of follow-up quality- adjusted life years (QALYs) will be calculatedo*Scar formation*: the following aspects of scar formation will be measured after 3, 6 and 12 months post burn:Scarring will be measured using the Patient and Observer Scar Assessment Score (POSAS), a valid and reliable scale that is designed for the evaluation of all types of scars by professionals and patients. It consists of two numeric scales: the Patient Scar Assessment Scale which is completed by the patient and the Observer Scar Assessment Scale which is completed by the medical staff. The variables scored by the patient are pain, itching, color, stiffness, thickness and irregularity [38–40]. The variables scored by the medical staff include vascularization, pigmentation, thickness, relief and pliabilityElasticity will be measured using a Cutometer (Courage & Khazak, Köln, Germany), a validated instrument to measure the vertical deformation of the skin in millimetres when the skin is pulled by means of a controlled vacuum into a circular aperture [41]Scar color and pigmentation will be measured using the DSM II colorimeter (Dermaspectrometer).This is a validated instrument to measure scar color by a narrow-band simple reflectance meter [41]o*Total (medical and non-medical) costs:* total costs in this study represent direct health care costs (inpatient and outpatient medical costs), direct non-healthcare costs and indirect non-health care costs (productivity loss). Personnel time and used materials for wound care and surgical procedures, hospital days for initial stay and re-admittance and outpatient visits during the first year will be measured prospectively as part of the case record form. Health resource use outside the hospital, travel costs and productivity losses will be recorded by questionnaires filled out by the patients at 3, 6 and 12 months post burn. Cost of dressing changes and surgical procedures will be assessed by translating the personnel time and used materials into costs by means of gross salaries and market prices. The costs of hospital stay and outpatient care in burn centers will be calculated by multiplying the number of hospital days respectively outpatient visits with their cost prices [42]. Other healthcare use will be translated into costs by standard prices [43]. Productivity losses will be valued using the friction cost method [44]o*Baseline parameters:* age, gender, skin type, wound etiology, bacterial contamination at admission, location of the wound, type of wound, TBSA% and co-morbidities. In all patients, the burn depth of the study area will be accurately determined on day 2–5 post burn by clinical evaluation and LDI scan using the moorLDI2-Burn Imager™ (Moor Instruments, Axminster, UK) and, based on pre-defined criteria (Table 1), be classified as superficial, intermediate or deep partial thickness injury. The size of each burn wound is then estimated in TBSA. In a LDI the low-intensity laser beam is scanned across a tissue surface in a raster fashion using a moving mirror. There is no direct contact with the tissue being assessed. The wounds are scanned by a trained research physician or nurse, after removal of topical medication (during regular wound treatment). All research physicians and nurses in both burn centers have followed the same training sessions and have the same experience. The scanning will take 1–5 minutes.

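### The supporting Cox model is run only if baseline looks unbalanced; it should be prespecified on prognostic grounds and fitted whatever the balance

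*Protocol article*

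**What the plan says.** Under Statistical analysis, the protocol article says that healing times in the two arms "will be analyzed with Kaplan-Meier curves and log rank test". No covariate or stratification factor is attached to that test.

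The next paragraph adds a second analysis under a condition: "If the baseline characteristics seem unbalanced despite randomization, a multivariable Cox regression analysis will be performed to correct for potentially confounding variables". Its purpose is "to correct for potentially confounding variables to confirm the primary analysis". No criterion for imbalance is given, and no variables are named.

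Under Secondary outcomes/study parameters, the baseline parameters are "age, gender, skin type, wound etiology, bacterial contamination at admission, location of the wound, type of wound, TBSA% and co-morbidities". The same item then adds laser Doppler imaging (LDI): "burn depth of the study area will be accurately determined on day" 2–5 post burn, after which the wound is to "be classified as superficial, intermediate or deep partial thickness injury". Randomization is stratified by center (Recruitment, consent and randomization), and that section also says that patients and treating staff cannot be blinded.

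**The concern.** Randomization already protects the unadjusted comparison against systematic confounding, so any baseline difference is a chance event. Adjustment is worth making for a variable that predicts healing, because leaving out such a variable pulls the marginal log hazard ratio toward zero and costs power. That holds whether or not the variable looks balanced. An unbalanced variable with no bearing on healing needs no adjustment.

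The stated rule uses the other criterion. Someone must look at the baseline table, decide whether it appears unbalanced and pick the variables, in a trial where treatment is known to those involved. What is at stake is the credibility and usefulness of the adjusted estimate, not the validity of the primary test.

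**Working it through.** **The plan's own figure.** The plan gives no figure for adjustment. The nearest is 41 per arm (Sample size calculation: 11 vs 6 days, SD 7.5, alpha 5%, 80% power). The two-means formula gives n = 2 × [7.5 × (1.960 + 0.842) / 5]² = 35.3, so 36 per arm. The stated 41 is met with an unstated step, for example a rank-test allowance (35.3 / 0.864 = 40.9). The difference is conservative and does not bear on this point. I use 2 × 41 = 82 patients below.

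**How often chance alone pulls the trigger.** Nine baseline variables are listed. If they are taken as independent and imbalance is read as a small p-value:
- at p<0.05: 1 − 0.95⁹ = 0.37
- at p<0.10: 1 − 0.90⁹ = 0.61

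At p<0.10, any given variable is picked in about 10% of trials, however strongly it predicts healing. A strong predictor is therefore left out about nine times in ten.

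**What the trigger recovers.** The simulation had 82 patients, about 10% censoring, 3,000 runs per scenario, Weibull healing times with shape 2 and a conditional hazard ratio of 1.8. There was one strong three-level prognostic factor, one weaker factor and five irrelevant variables. The trigger was p<0.10 on any of the seven; if it did not fire, the log-rank result stood. It fired in 53–55% of runs, against 1 − 0.90⁷ = 52% expected.

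| HR per level of the strong factor | Log-rank | Triggered Cox | Prespecified Cox |
|---|---|---|---|
| about 1.6 | 55.8% | 56.2% | 68.5% |
| about 2.7 | 42.4% | 42.7% | 67.9% |
| about 4.5 | 32.1% | 33.3% | 67.9% |

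The trigger adds 0.3 to 1.2 percentage points. Prespecified adjustment adds 12.7, 25.5 and 35.8. The mean estimated log hazard ratio was 0.51, 0.42 and 0.36 unadjusted, and about 0.62 adjusted.

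**Error rate with no treatment effect.** Log-rank 4.9–5.2%; triggered rule 3.7–4.5%; prespecified Cox with a Wald test 5.6–6.3%. The Monte Carlo standard error is about 0.4 points, so a small part of the prespecified gain reflects a slightly liberal Wald test.

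**Limits of the simulation.** The strong factor was modelled on burn depth classes, which are not in the list recommended below. A hazard ratio of 1.8 with shape 2 multiplies times by 1.8^(−1/2) = 0.745, about 2.8 days off an 11-day mean and not the planned 5. The table compares one adjustment rule with another. It does not estimate power for this trial.

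**Timing of LDI depth.** Admission is within 48 hours of injury (Study population). Flaminal starts within 24 hours of admission (Interventions; no start time is given for the other arm). Its latest start is therefore 48 + 24 = 72 hours after injury, while the scan is on day 2–5. The scan is made after topical medication is removed, and Table 2 places it in the treatment phase. Depth can therefore be a post-treatment measurement, although it is described with the baseline parameters.

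**The case against.** The strongest reply is that the Cox model is declared confirmatory. The log-rank test is run whatever the balance, is valid without adjustment and keeps its error rate. An article may also leave the covariate list and the imbalance criterion to a fuller document. Both points stand. The missing list alone would be no finding, and that the variables are picked after seeing the data is an inference from the trigger and the absence of names. The trigger itself is different: it is a stated rule, and a later document could repair it only by replacing it.

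Three stronger readings are tempting, and the documents do not support them.

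- *A reader might infer that false positives are inflated.* In the simulation, free choice among unadjusted, single-covariate, triggered and two-covariate results gave 11–14%. The plan does not allow that choice for its primary conclusion, and the triggered rule alone stayed below 5%.
- *A reader might take the depth classes in Table 1 and claim a large, quantified power loss.* That would measure adjustment for depth, which should not be in the main model. Reading 11/6 = 1.83 as a hazard ratio also holds only for exponential times. With Weibull shape 3 it shortens healing by just 18% (1.83^(−1/3) = 0.82), about 3 days under assumed class medians of 10, 17 and 26 days, not the planned 5.
- *A reader might infer that the plan will adjust for LDI depth and so remove a treatment effect.* The Statistical analysis section never names depth as a covariate. The timing is a caution only.

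**Conclusion.** The point holds as one about a supporting analysis. The protocol ties adjustment to observed imbalance, which is the wrong criterion in a randomized trial, and leaves to chance and judgement whether the adjusted result exists and what it contains. The primary test's type I error is not affected.

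That the trigger recovers almost none of the available power rests on the simulated set-up: a p<0.10 trigger, seven independent variables and assumed effects. The reason behind it is general, because selection by imbalance ignores prognostic strength. How much this trial would gain is unknown. The documents give no prognostic strength for age, TBSA%, etiology or wound location, so the gain runs from none upward. The change is worth making because it costs almost nothing and removes a choice, not because a given loss of power has been shown.

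**What to change.** Replace the conditional sentence with an unconditional one. Suggested wording: *A Cox model for time to re-epithelialization, stratified by center, with treatment, age, TBSA%, etiology and wound location as covariates, will be fitted and reported alongside the log-rank test regardless of baseline balance.* The four covariates are an example. What matters is that the list is short, is chosen for expected prognostic value, uses only data collected at admission, and has its categories fixed in advance.

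Keep the log-rank test as primary. If LDI depth is used at all, put it in a separately labelled sensitivity analysis, with a note that it can be measured after treatment has started.

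The cost is about one sentence, and every variable is already collected. The Trial status section reports that recruitment is complete, so the list should be dated before healing times are compared by arm. If that comparison has already been made, the model should be labelled post hoc.
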